### Duration of treatment period and follow-up

In the both the clinical and public pilots, patients will be recruited for a period of 7 months, and treated and followed up for 6 months.

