### Measures: baseline and outcome and process measures

The clinical pilot and public pilot are different interventions with shared metrics and also exclusive ones to each case. The primary outcome, the smoking cessation rates, will be measured at the 60, 120, and 180-day follow-up time points, using the urinary cotinine and expired carbon monoxide levels in the clinical pilot case, and the self-reported questionnaires in the public pilot case. To assess the secondary outcomes, different metrics are required. Table 2 includes information about how they will be calculated, to which other metrics they will be compared, and to which pilot they are related.

**Table 2 Tab2:** Description of metrics to assess the primary and secondary outcome

Metric	Calculation	Comparisons	Pilot	Related secondary outcome
Primary outcome				
Smoking cessation rate	Total number of people who relapsed / total number of people in the group at 60 days, 120 days, and 180 days of their quitting date	• User engagement at an individual level • User engagement at an aggregated level • User mobile app usage • User quitting attempts • User lifestyle feedback • Physical activity	• Clinical • Public	System influence on smoking cessation and app influence on users physical activity levels
Secondary outcomes				
User engagement at an individual level	Messages read by the user / total number of messages sent to the user	• Smoking cessation rate	• Public • Clinical	System influence on smoking cessation
Engagement at an aggregated level	Mobile application rolling retention, session length distribution, session frequency, sessions per user, return rate	• Smoking cessation rate	• Public • Clinical	System influence on. smoking cessation.
User quitting attempts	Number and date of quitting attempts	• Smoking cessation rate	• Public • Clinical	System influence on smoking cessation
User app behavior	Time spent per app section	• User message ratings • User satisfaction with messages	• Public • Clinical	App usage. and opinions on messages the users received
User satisfaction with messages	Satisfaction questionnaire	• User mobile app usage • Mobile app behavior • User message ratings	• Clinical	App usage and opinions on messages the users received
User message ratings	Users’ votes for each message on a 5-star scale	• User app behavior	• Public • Clinical	App usage and opinions on messages the users received

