User lifestyle feedback	Comparison of changes in user lifestyle (at baseline and after 6 months) through the questionnaires: EQ-5D-5 L, IPAQ for physical activity, and SF-36	• Smoking cessation rate • Mobile app usage	• Clinical	App influence on users physical activity levels
Physical activity	Total time (min) of activity per user, retrieved by GoogleFit	• Smoking cessation rate • Mobile app usage	• Public • Clinical	App influence on users physical activity levels

*EQ-5D-5 L* EuroQol 5-dimension 5-level questionnaire, *IPAQ* International Physical Activity Questionnaire, *SF-36* Short Form 36-item Health Survey

Although they are not necessary to the assessment of the primary and secondary outcomes, the metrics described in Table 3 will also be retrieved and analyzed because they are considered relevant and potentially useful.

**Table 3 Tab3:** Description of additional metrics to be measured in the study

Metric	Calculation	Pilot
User reliability	Comparison of the abstinence self-report at 2-week intervals with the measurements of the CO-oximeter	Clinical
QALY (financial aspects)	Healthcare resource utilization and cost analysis (cost of devices used, pharmacological treatment and time spent for various purposes)	Clinical
Precision of the recommender system	Messages sent and rated more than four stars / total number of rated messages	Public Clinical
Smoke-free period	Time range between quitting date and the last smoke-free report	Clinical

*CO* carbon monoxide, *QALY* quality-adjusted life year

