### Statistical analysis

In the clinical pilot, patients will be classified as either smokers or non-smokers according to their positive or negative values in the urine test and the expired CO tests (PiCO values between 0 and 6 will be considered non-smokers) at each follow-up visit. In case of discrepancy between tests, we will consider the patient as a smoker. We will perform repeated analysis of variance (ANOVA), and provide *p* values, to compare the number of non-smokers in the intervention versus control group at 2 months, 4 months and 6 months of their quitting day.

In the public pilot, users will be considered to be non-smokers according to their self-reported answer to the question: “Are you still resisting the temptation or have you smoked? Please, be honest.” We will perform repeated ANOVA, and provide *p* values, to compare the number of non-smokers in the intervention versus control group every 2 weeks.

For secondary outcomes, the numerical variables (user engagement at aggregated level, user mobile app usage, user quitting attempt, user app behavior, and user lifestyle feedback EuroQoL 5 dimensions 5 levels questionnaire (EQ-5D-5 L) and Short Form 36-item Health Survey (SF-36), and physical activity) will be assessed with *T* tests and variance ANOVA tests. Categorical variables (user engagement at individual level, user satisfaction with messages, user message ratings, and lifestyle answers to the International Physical Activity Questionnaire (IPAQ)) will be assessed with chi-square tests. In addition, we intend to study the combination of all metrics with a linear regression analysis, and the Kaplan-Meier method to analyze the overall survival rate (non-smokers). All tests will be two-tailed and with a significance level set at 0.05. All analyses will be done according the intention-to-treat principle, and using the SPSS software version 25. Missing data will be calculated with the last observation carried forward.

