**Fig. 3 Fig3:**
[figure not shown]
Screenshots of the app (English and Mandarin versions) showing different sections

A nurse will provide patients with instructions for downloading and using the app. Questions related to the patient’s basic demographic information and an extended profile (including social influences, plan of action, skills, attitudes, and self-efficacy with regard to smoking) will be assessed in the app.

The data obtained from the database will be analyzed in a comma-separated value (CSV) format using SPSS software.

Users’ physical activity data will be collected using their mobile phones. The mobile app will use GoogleFit [40] to track daily physical activity. These data will be available to users through the GoogleFit app but not displayed within the 3M4Chan app, as it will be utilized for research purposes only.

Patients will be followed up after 60, 120, and 180 days of their initial consultation with a variance margin of 5 days. In the initial consultation, the patient will be assessed in the smoking cessation unit after they have been referred from either the pneumology unit or another clinical department. Smoking-related symptoms, treatment adherence, daily cigarette use, and possible adverse events will be discussed and exhaled carbon monoxide, urinary cotinine, and other clinical information, such as weight and height, will be assessed. Quality of life (EQ-5D-5 L, IPAQ, and SF-36) questionnaires will also be collected. The patient will be instructed on relaxation techniques and on tips to avoid smoking.

During the second consultation, physicians will gather patient information on smoking-related symptoms, treatment adherence, daily cigarette use, possible adverse events, exhaled carbon monoxide and urinary cotinine levels, and other clinical information. Coaching for relapse prevention will be performed.

At the third consultation, information about smoking-related symptoms, treatment adherence, possible adverse events, exhaled carbon monoxide and urinary cotinine levels, and other clinical information will again be collected. New relaxation techniques will be explained if the previously taught techniques have not been effective. Techniques for relapse prevention will be reviewed. It will also be collected the users’ physical and psychological health state, their exhaled carbon monoxide levels, the results from a urinary cotinine test, and will be asked clinical information such as weight and height.

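### The smoke-free period in Table 3 has no stop at relapse, so with a single fixed quitting date it counts time spent smoking as smoke-free

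*Protocol article*

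**What the plan says.** Table 3 (section on baseline, outcome and process measures) defines the smoke-free period, for the clinical pilot only, as "Time range between quitting date and the last smoke-free report". The sentence introducing Table 3 ranks its metrics below the main outcomes: "Although they are not necessary to the assessment of the primary and secondary outcomes", they will still be collected and analysed as potentially useful.

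Four other statements bear on how the definition works:

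- Table 2 lists quitting attempts as a secondary metric for both pilots, calculated as "Number and date of quitting attempts".
- Patients are "treated and followed up for 6 months" (Duration of treatment period and follow-up). The Materials section gives the clinic schedule: "Patients will be followed up after 60, 120, and 180 days of their initial consultation with a variance margin of 5 days".
- Table 3 also mentions fortnightly self-reports, under user reliability: "Comparison of the abstinence self-report at 2-week intervals with the measurements of the CO-oximeter".
- The Statistical analysis section classifies clinical patients as smokers or non-smokers separately at each follow-up visit, from the urine and expired carbon monoxide tests: "In case of discrepancy between tests, we will consider the patient as a smoker".

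In Table 2 and in the Statistical analysis section, the assessment times of the cessation rate are counted from each patient's quitting date or day, in the singular.

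**The concern.** The definition fixes the end of the period by the last smoke-free report alone. What was reported before it plays no part. The article does not require the smoke-free reports to be unbroken, and it does not subtract time spent smoking.

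The definition fails in a situation that the protocol itself expects. The Background calls relapse after quitting highly probable, Table 2 records the dates of several attempts, and a non-smoker result at one visit does not depend on the result at the visit before. A patient can therefore relapse, try again and give a smoke-free report late in follow-up. With one fixed quitting date, that patient gets the same value as a patient who never smoked after quitting. The metric would then not measure what its name says, and descriptive summaries of abstinence duration would be too long for patients who relapse and quit again.

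**Working it through.** The article gives no figure for this metric, so there is nothing to reproduce. The check applies the definition to example sequences.

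**Inputs.** Clinic visits at days 60, 120 and 180, each within 5 days (Materials); self-reports every 14 days (Table 3); follow-up of 6 months, taken as 180 days. Assumption: one quitting date, at day 0 of this schedule. The sequences are illustrations, not data from the protocol.

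**Formulas.**
- As written: day of the last smoke-free report minus quitting date.
- Comparator: day of the last smoke-free report before the first report or test showing smoking, minus quitting date.

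**Clinic visits only.** Smoke-free at 60, smoking at 120, smoke-free at 180:
- As written: 180 − 0 = 180 days.
- Comparator: 60 − 0 = 60 days.
- Difference: 180 − 60 = 120 days. With the 5-day margin at both visits it lies between 175 − 65 = 110 and 185 − 55 = 130 days.
- If the quitting date falls *q* days after the first consultation (*q* below 60), both values drop by *q* and the difference stays at 120 days.

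**Fortnightly reports plus day 180.**

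| Sequence of reports | As written | Comparator |
|---|---|---|
| Smoke-free throughout | 180 | 180 |
| Smoke-free to day 56, smoking from then on | 56 | 56 |
| Smoking reported on days 70 to 126, otherwise smoke-free | 180 | 56 |
| Smoke-free on day 14, smoking reported on days 28 to 168, smoke-free on day 180 | 180 | 14 |

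In the third row the intervals that end in a smoking report cover 126 − 56 = 70 days; in the fourth, 168 − 14 = 154 days. All of them count as smoke-free under the definition as written.

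The two rules agree whenever no smoke-free report follows a relapse. Where one does, the definition as written gives the longer value. With a fixed quitting date at day 0, any patient smoke-free at day 180 scores 180 days whatever happened earlier.

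**The other reading of quitting date.** Suppose the date is reset at each new attempt. In the clinic-visit example the new attempt starts at some day *t* between 120 and 180, so the value is 180 − *t*, at most 60 days. The overstatement goes, but the first smoke-free stretch is lost. The same patient thus scores 180 days under one reading and at most 60 under the other.

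**The case against.** The strongest reply is that the article does not say that the quitting date is that of the first attempt. Since Table 2 records several attempts, each with a date, the period could be meant to run from the current one, and then most of the overstatement disappears. This stands as a limit on certainty. It does not remove the point: Table 2 and the Statistical analysis section treat the quitting date as one date per patient, Table 3 mentions no reset, and the two readings give very different values. Nor is this only a detail left to a fuller document, because the article states a calculation, and under its more natural reading that calculation gives a wrong value.

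The second reply is that the metric is peripheral. This stands in full. It is an additional metric in one pilot, and the clinical primary outcome rests on cotinine and carbon monoxide at each visit. The Statistical analysis section names no between-group test of it; only the general regression on all metrics combined might include it. The planned Kaplan-Meier analysis is not linked to it.

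A reader might go further and infer that the definition would make the app appear to prolong abstinence, because the Discussion expects longer abstinence in support of the hypothesis. The documents do not support that step. The stated hypothesis concerns cessation rates, the Discussion does not name this metric among those that will validate it, no comparison of it between arms is planned, and nothing says that the app prompts new attempts after a relapse.

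A reader might also take a large ratio from an extreme sequence as the size of the error. No figure in the article says how often any of these sequences occurs, and the ratio depends on the sequence chosen and on how often patients report.

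**Conclusion.** The point holds as a minor one. As written, the smoke-free period has no stop at relapse. With a single fixed quitting date it counts smoking time as smoke-free for every patient who relapses and later gives a smoke-free report. On the protocol's own visit schedule, one such pattern scores 180 days against 60.

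This rests on two assumptions: that the quitting date is one date per patient, which the wording suggests but does not state, and that some patients relapse and quit again, which the protocol foresees without giving a frequency. The average effect on the metric therefore cannot be calculated from the article. The primary outcome, its test and the sample size do not depend on this metric.

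**What to change.** Change the calculation cell for the smoke-free period in Table 3 to one of two rules, and state which:

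1. The period runs from the quitting date to the last smoke-free report before the first report or test showing smoking. If there is none, it is censored at the last assessment.
2. The period is counted separately for each quit attempt, from that attempt's own date.

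Under the first rule, report later attempts under the existing quitting-attempts metric. Under either rule, say whether a report means the fortnightly self-report, the clinic test or both, since this determines the dates used.

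The cost is one table cell and a sentence. The first rule can be applied with the clinic assessments that both arms receive. The second needs dated quit attempts in both arms. Table 2 lists these for the clinical pilot, but Table 1 shows only the cessation rate for the clinical control group, which does not receive the app. The sponsor should therefore confirm that those dates are recorded for controls before choosing the second rule.

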### Statistical analysis

In the clinical pilot, patients will be classified as either smokers or non-smokers according to their positive or negative values in the urine test and the expired CO tests (PiCO values between 0 and 6 will be considered non-smokers) at each follow-up visit. In case of discrepancy between tests, we will consider the patient as a smoker. We will perform repeated analysis of variance (ANOVA), and provide *p* values, to compare the number of non-smokers in the intervention versus control group at 2 months, 4 months and 6 months of their quitting day.

In the public pilot, users will be considered to be non-smokers according to their self-reported answer to the question: “Are you still resisting the temptation or have you smoked? Please, be honest.” We will perform repeated ANOVA, and provide *p* values, to compare the number of non-smokers in the intervention versus control group every 2 weeks.

For secondary outcomes, the numerical variables (user engagement at aggregated level, user mobile app usage, user quitting attempt, user app behavior, and user lifestyle feedback EuroQoL 5 dimensions 5 levels questionnaire (EQ-5D-5 L) and Short Form 36-item Health Survey (SF-36), and physical activity) will be assessed with *T* tests and variance ANOVA tests. Categorical variables (user engagement at individual level, user satisfaction with messages, user message ratings, and lifestyle answers to the International Physical Activity Questionnaire (IPAQ)) will be assessed with chi-square tests. In addition, we intend to study the combination of all metrics with a linear regression analysis, and the Kaplan-Meier method to analyze the overall survival rate (non-smokers). All tests will be two-tailed and with a significance level set at 0.05. All analyses will be done according the intention-to-treat principle, and using the SPSS software version 25. Missing data will be calculated with the last observation carried forward.

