**Methods:**

Our study will gather data from two sources. The first source is a clinical pilot in which a group of patients from two Taiwanese medical centers will be randomly assigned to either an intervention or a control group. The intervention group will be provided with a mobile app that sends motivational messages selected by a recommender system that takes the user profile (including gender, age, motivations, and social context) and similar users’ opinions. For 6 months, the patients’ smoking activity will be followed up, and confirmed as “smoke-free” by using a test that measures expired carbon monoxide and urinary cotinine levels. The second source will be a public pilot in which Internet users wanting to quit smoking will be able to download the same mobile app as used in the clinical pilot. They will be randomly assigned to a control group that receives basic motivational messages or to an intervention group, that receives personalized messages by the recommender system. For 6 months, patients in the public pilot will be assessed periodically with self-reported questionnaires.

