### Inclusion/exclusion criteria

In order to be eligible for the clinical pilot study, each patient has to meet the following inclusion criteria. Participants will be required to be a current smoker aged 20 years or older who owns an Android mobile phone and is able to read Mandarin. Additionally, only those who have smoked at least once per month for the past 2 years and are willing to share information from their medical Electronic Health Record (EHR) with project researchers will be considered. Furthermore, patients will be required to sign an informed consent and agree to be followed up for 6 months.

For the public pilot study, all interested people who download the 3M4Chan app in their Android smartphone, who are aged 20 years or older, and who can read English or Mandarin will be able to join.

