At the fourth consultation, physicians will collect information about smoking-related symptoms, treatment adherence, and possible adverse events. Techniques for avoiding the risk of relapse are reinforced. Data about blood pressure, weight, height, and quality of life (using EQ-5D-5 L, IPAQ, and SF-36 questionnaires as well as a questionnaire assessing the satisfaction about the motivational messages received through the 3M4Chan app) will also be collected. All input clinical data will be checked for correctness by two healthcare professionals to ensure quality.

The public pilot will use the same mobile app as the clinical pilot. No additional materials will be used.

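### The clinical pilot scores non-smoker status from two spot tests alone, so a patient who reports smoking, or a light smoker who has not changed, can count as a success when both tests are negative

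*Protocol article*

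**What the plan says.** The protocol article's Measures section says the primary outcome is assessed at 60, 120 and 180 days, "using the urinary cotinine and expired carbon monoxide levels in the clinical pilot case"; self-reported questionnaires are named for the public pilot only. The Statistical analysis section turns this into a rule: patients are "classified as either smokers or non-smokers according to their positive or negative values in the urine test and the expired CO tests". For carbon monoxide (CO), "PiCO values between 0 and 6 will be considered non-smokers". One tie-break is given: "In case of discrepancy between tests, we will consider the patient as a smoker".

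Table 2 calculates the primary outcome from the number of people who relapsed, at 60, 120 and 180 days from the quitting date.

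The Inclusion/exclusion criteria admit current smokers, and among them "only those who have smoked at least once per month for the past 2 years". No positive CO or cotinine result at baseline is required.

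Self-report is collected in the clinical pilot. Table 3 lists an abstinence report at 2-week intervals, to be compared with the CO reading, but the sentence introducing that table says its metrics are not needed to assess the primary and secondary outcomes. In the Materials section, daily cigarette use is listed for the initial and second consultations. The third lists "information about smoking-related symptoms, treatment adherence, possible adverse events, exhaled carbon monoxide and urinary cotinine levels" without cigarette use. At the fourth, "physicians will collect information about smoking-related symptoms, treatment adherence, and possible adverse events", again without it.

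**The concern.** The outcome is meant to show who has stayed off cigarettes since the quit date. Two spot tests at three visits show only whether smoking was recent enough to be detected. Two kinds of patient can pass without having stopped:

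- **The admitted relapser.** The patient reports smoking between visits, but both tests are negative on the day. The tie-break covers test against test, not test against report, so the patient is scored a non-smoker. This can happen at any level of smoking.
- **The light smoker.** The entry floor is once a month. Such a patient can be negative on both tests at the initial consultation and at each follow-up visit with no change in behaviour, so the entry and success criteria overlap.

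At stake is the meaning of the clinical pilot's primary outcome. Counted successes may include people who have not quit, which raises the cessation rates and may shrink the difference between arms.

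**Working it through.** **1. The rule, followed through.** The possible combinations at a follow-up visit are:

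| Urine test | CO | Patient's report | Status under the protocol |
|---|---|---|---|
| negative | 0–6 | no smoking | non-smoker |
| negative | 0–6 | has smoked | non-smoker |
| one test positive, the other negative | | either | smoker (tie-break) |
| positive | above 6 | either | smoker |

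The second row is the problem. Nothing in the Measures section, Table 2, Table 3 or the Statistical analysis section changes it.

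**2. The plan's own figure.** The sample size section assumes 0.2 against 0.5, two-sided alpha 0.05 and power 0.80, and states 45 per group. The two-proportion formula gives 39 per group without continuity correction and 45 with it, so 45 is reproduced. At the planned 50 per arm, power is 89% (normal approximation, no correction, here and below).

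**3. Chance that an unchanged light smoker tests negative.** Assumptions, none from the documents: smoking on one random day in 30, and tests that detect smoking for w days.

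- One visit: 1 − w/30. For w = 1, 0.967; w = 3, 0.900; w = 5, 0.833.
- All three visits, treated as independent: (1 − w/30)³ = 0.903, 0.729 and 0.579.
- Share of follow-up that the tests can see: 3w/180, which is 1.7% for w = 1 and 8.3% for w = 5.

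**4. What this could do to the comparison.** This depends on a further assumption about who is misclassified.

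(a) *Same number of points added to both arms.* Suppose 10% of each arm (5 of 50) are such smokers and none quits. Each arm's rate then rises by 0.10 × 0.833 = 0.083 to 0.10 × 0.967 = 0.097. The rates become about 0.28 to 0.30 against 0.58 to 0.60. The difference stays at 0.30, and power at 50 per arm is about 87%.

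(b) *Same share f of true smokers misclassified in both arms.* Then p′ = p + f(1 − p), and the difference is 0.30 × (1 − f).

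| f (assumed) | Rates | Difference | Power at 50 per arm |
|---|---|---|---|
| 0 | 0.20 v 0.50 | 0.30 | 89% |
| 0.05 | 0.24 v 0.525 | 0.285 | 85% |
| 0.10 | 0.28 v 0.55 | 0.27 | 79% |
| 0.20 | 0.36 v 0.60 | 0.24 | 68% |

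The documents give no value for w, for the share of light smokers or for f. The results in (a) and (b) illustrate the mechanism and are not estimates.

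**The case against.** **The tests are strict and objective.** Either positive test makes the patient a smoker, and a biochemical endpoint suits a trial whose care providers are not blinded. This stands in part. A reader might infer that every admitted or monthly smoker is counted as a success. The rule does not do that; they pass only when both tests are negative at that visit.

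**The patient's account is collected.** This is correct. From the consultation lists a reader might infer that no self-report exists at days 120 and 180, but Table 3 provides 2-weekly reports. Nor do the lists prove that cigarette use is not asked: the fourth consultation's list also omits CO and cotinine, which the outcome needs at 180 days, so the lists are either incomplete or in conflict with the analysis section. What remains is that the reports are collected but set aside for the primary outcome.

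**The abstract implies verification of reported status.** It says smoking activity is followed up and confirmed as smoke-free "by using a test that measures expired carbon monoxide and urinary cotinine levels". That can be read as tests confirming a report, but it contains no rule making a patient who reports smoking a failure. The analysis section does state a rule, with a tie-break, and leaves the report out. This is therefore not detail left to an unseen document.

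**The size is not shown.** This stands. Once a month is a floor, and patients attending smoking cessation units may mostly smoke far more. A reader might infer a known inflation of 8 to 10 points that distorts the comparison. That figure rests on two assumed inputs, and added equally to both arms it leaves the planned difference unchanged. The direction is not settled either. The Materials section lists nicotine patches, gum and inhalers; if these can turn the urine test positive, which the documents do not address, some abstinent patients would be scored as smokers.

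**Conclusion.** The concern holds as a defect in the stated outcome rule. Followed as written, the rule scores a patient who reports relapse as a non-smoker if both tests are negative, and it lets a light smoker meet the success criterion from entry onwards. That sits badly with Table 2's relapse-based outcome.

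The size is unknown. Under an assumed detection window of 1 to 5 days, an unchanged one-day-in-30 smoker passes a single visit with probability 97% to 83% and all three with probability 90% to 58%. The effect on the arm difference ranges from none, if equal points are added to both arms, to a fall from 0.30 to 0.24, if 20% of true smokers are misclassified. The documents do not support a claim that the comparison is distorted by a known amount. The change is still worth making: negative tests stay necessary, so adding the report can only remove successes, and it costs little.

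**What to change.** 1. In the Statistical analysis section, count a patient as a non-smoker at a visit only if the patient reports no smoking over a pre-stated window and both tests are negative. Reported smoking with negative tests counts as smoker. A 30-day window is one option; it makes smoking at the entry floor count as smoking. Ask the question in the same words in both arms at all three follow-up visits, and list it, with CO and cotinine, for each of those consultations.

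2. Pre-specify a sensitivity analysis that excludes patients who already meet the non-smoker test criterion at the initial consultation. CO and cotinine are already taken there, so no new test is needed.

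3. Align Table 2 with the chosen definition, since its numerator counts people who relapsed under the name of a cessation rate.

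Cost: one question at existing visits and a few sentences of text. Cessation rates will come out somewhat lower, and the outcome gains a self-reported component in a trial with unblinded care providers. Asking identically in both arms limits differential reporting but does not remove it, so the tests-only result should be reported alongside.
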